## Abstract

**Background:**

The International Association of Diabetes and Pregnancy Study Groups (IADPSG) recommends universal screening with a 75 g oral glucose tolerance test (OGTT) using stricter criteria for gestational diabetes (GDM). This may lead to important increases in the prevalence of GDM and associated costs, whereas the gain in health is unclear. The goal of ‘The Belgian Diabetes in Pregnancy Study’ (BEDIP-N) is to evaluate the best screening strategy for pregestational diabetes in early pregnancy and GDM in an ethnically diverse western European population. The IADPSG screening strategy will be followed, but in addition risk questionnaires and a 50 g glucose challenge test (GCT) will be performed, in order to define the most practical and most cost effective screening strategy in this population.

**Methods:**

BEDIP-N is a prospective observational cohort study in 6 centers in Belgium. The aim is to enroll 2563 pregnant women in the first trimester with a singleton pregnancy, aged 18–45 years, without known diabetes and without history of bariatric surgery. Women are universally screened for overt diabetes and GDM in the first trimester with a fasting plasma glucose and for GDM between 24–28 weeks using the 50 g GCT and independently of the result of the GCT, all women will receive a 75 g OGTT using the IADPSG criteria. Diabetes and GDM will be treated according to a standardized routine care protocol. Women with GDM, will be reevaluated three months postpartum with a 75 g OGTT. At each visit blood samples are collected, anthropometric measurements are obtained and self-administered questionnaires are completed. Recruitment began in April 2014.

**Discussion:**

This is the first large, prospective cohort study rigorously assessing the prevalence of diabetes in early pregnancy and comparing the impact of different screening strategies with the IADPSG criteria on the detection of GDM later in pregnancy.

**Trial registration:**

ClinicalTrials.gov: NCT02036619. Registered 14-1-2014.

## Background

Gestational diabetes (GDM) is a frequent medical condition during pregnancy and was historically defined as ‘any degree of glucose intolerance with onset or first recognition during pregnancy’ [1]. GDM has long been known to raise the risk of a large for gestational age (LGA) baby and macrosomia resulting in increased rates of shoulder dystocia and caesarian deliveries [2,3]. Shortly after the delivery the glucose values are generally restored to normal, but women with GDM have a seven-fold increased risk of developing type 2 diabetes (T2DM) [4]. The initial criteria for diagnosis of GDM were established more than 40 years [5]. These criteria were chosen to identify women at high risk for development of diabetes after pregnancy and not necessarily to identify pregnancies with increased risk for adverse perinatal outcome [6].

Meanwhile, two large randomized intervention trials have demonstrated improvement in perinatal outcomes in the group of women who received treatment of mild glucose intolerance during pregnancy, especially in the frequency of LGA [7,8]. Lack of international uniformity in the approach to ascertainment and diagnosis of GDM has been a major hurdle to compare the results of both studies. The ACHOIS study used a 75 g oral glucose tolerance test (OGTT) using the former WHO criteria for GDM while the study of Landon et al. used a 3-hour OGTT with the Carpenter & Coustan criteria for GDM [7,8]. Progressively more data have shown that the risk of adverse perinatal outcomes is also associated with degrees of hyperglycaemia less severe than overt diabetes during pregnancy. The ‘Hyperglycemia and Adverse Pregnancy Outcome Study’ (HAPO), showed a continuous and graded relationship between maternal hyperglycaemia and the risk for an adverse perinatal outcome, independent of other risk factors [2].

In June 2008, the ‘The International Association of Diabetes and Pregnancy Study Groups’ (IADPSG) organized a conference leading to a new consensus statement for a new screening strategy and diagnosis of GDM [9]. Women with overt diabetes are at an increased risk for congenital anomalies and diabetes complications due to their greater degree of hyperglycaemia earlier in pregnancy [10]. The IADPSG advises therefore to screen for existing but unknown diabetes at the first prenatal clinic visit, especially in high risk populations. Cut-offs for tests used to detect diabetes in the non-pregnant population are recommended in early pregnancy [fasting plasma glucose ≥ 126 mg/dl (7.0 mmol/l), random plasma glucose ≥ 200 mg/dl (11.1 mmol/l) or HbA1c ≥ 6.5% (47 mmol/mol)]. If overt diabetes or GDM has not been diagnosed in early pregnancy or enrollment is at 24 weeks gestation or later, IADPSG advises that every woman should undergo a 75 g OGTT. The cut-off values for the FPG, 1-h and 2-h OGTT were chosen to reflect an increase in risk of 75% for the development of a birth weight > 90th percentile, an umbilical cord C-peptide in the baby > 90th percentile and percentage body fat in the baby > 90th percentile. One abnormal value is now enough to diagnose GDM [FPG ≥ 92 mg/dl (5.1 mmol/l); 1-h plasma glucose ≥ 180 mg/dl (10 mmol/l); 2-h plasma glucose ≥ 153 mg/dl (8.5 mmol/l)]. By these new criteria, the total incidence of GDM in the HAPO cohort was 16.1% but with a substantial variation among sites, ranging from 8.7% in Israel and 23.7% in the US [11]. It is generally considered that there is not enough evidence to recommend screening and treatment of GDM before 24–28 weeks of gestation. IADPSG recommends now that a FPG ≥ 92 mg/dl (5.1 mmol/l) in early pregnancy be classified as GDM [9]. This was mainly reached by consensus only and uses the cut-off derived from the HAPO study in the second part of pregnancy.

Internationally, the IADPSG recommendation for screening for GDM remains controversial since this will lead to an important increase in the prevalence of GDM, workload and associated costs. For instance, in a Norwegian population with 40% from ethnic minorities, GDM prevalence would increase from 13.0% with the former WHO criteria to 31.5% with the IADPSG criteria [12]. Other raised comments are the paucity of data on the cost effectiveness of such screening strategy, the uncertainty on the clinical relevance of treatment of mild GDM based on the IADPSG criteria and the uncertainty on the risk of women who have had mild GDM to develop T2DM postpartum [13-15]. If the IADPSG would have chosen the new criteria to be based on an odds ratio of 2.0 instead of 1.75 for the development of complications in the HAPO study, the threshold for abnormal values would have been higher [FPG ≥ 95 mg/dl (5.3 mmol/l); 1-h plasma glucose ≥ 191 mg/dl (10.6 mmol/l); 2-h plasma glucose ≥ 162 mg/dl (9.0 mmol/l)] leading to a much lower GDM prevalence in the HAPO study of 8.8% compared to 16.1% with the current IADPSG criteria [9]. Another problem is that an OGTT is a poorly reproducible test [16]. The diagnosis of GDM on the basis of one abnormal value and based on only 1 test, is consequently a point of discussion since when repeating the OGTT in the same women, the test could be completely normal.

So far, two studies have addressed the cost-effectiveness of GDM screening according to the IADPSG criteria using decision analysis models for a US population. One study showed that the IADPSG recommendations are cost effective only when post-delivery care reduces diabetes incidence [17]. In the second study management based on the IADPSG criteria would be effective if treatment would result in a decreased incidence of preeclampsia with more than 0.55% and in a decreased incidence of caesarean deliveries of more than 2.7% [18].

While the ADA has since December 2010 adopted the IADPSG recommendations, the American College of Obstetricians and Gynecologists (ACOG) and an independent expert panel assigned by the National Institute of Health (NIH) continue to promote to use of the two-step screening strategy, using an universal screening strategy with the non-fasting 50 g glucose challenge test (GCT) and if abnormal followed by the 3-hour 100 g OGTT using the Carpenter & Coustan criteria or the National Diabetes and Data Group criteria [19,20] [Table 1]. The panel assigned by the NIH was particularly concerned that the adoption of the IADPSG criteria would increase the prevalence of GDM, and the corresponding costs without clear demonstration of improvements in the most clinically important health and patient-centered outcomes. Recently both the WHO and the Endocrine Society revised their guidelines and advise now to implement the IADPSG screening strategy for GDM [21,22]. The latest 2014 ADA recommendations, specify that further research is needed to establish a uniform approach to diagnosing GDM and leave now open the option between the one-step IADPSG recommendation or the two-step screening strategy as recommended by the NIH Consensus Conference [23]. Table 2 gives an overview of the different international recommendations for screening for GDM.

**Table 1 T1:** An overview of the different diagnostic criteria for GDM

	**NDDG 3-hour 100 g OGTT**	**Carpenter & Coustan 3-hour 100 g OGTT**	**IADPSG 2-hour 75 g OGTT**
Fasting	≥105 (5.8)	≥95 (5.3)	≥92 (5.1)
1 h	≥190 (10.6)	≥180 (10.0)	≥180 (10.0)
2 h	≥165 (9.2)	≥155 (8.6)	≥153 (8.5)
3 h	≥145 (8.0)	≥140 (7.8)	
**The number of abnormal values needed for the diagnosis of GDM**	≥ 2	≥ 2	≥ 1

Values are presented in mg/dl (mmol/l). NDDG: National Diabetes Data Group; OGTT: oral glucose tolerance test; IADPSG: The International Association of Diabetes and Pregnancy Study Groups.

**Table 2 T2:** Overview of the different international recommendations for screening for GDM

**WHO**	➢ IADPSG criteria for GDM
**Endocrine Society**	➢ One-step screening strategy with IADPSG criteria
**ADA**	Option between:
	➢ One-step screening strategy with IADPSG criteria
	Or
	➢ Two-step screening strategy with 50 g GCT and 100 g OGTT with the Carpenter & Coustan criteria or the NDDG criteria
**NIH**	➢ Two-step screening strategy with 50 g GCT and 100 g OGTT with the Carpenter & Coustan criteria or the NDDG criteria
**ACOG**	➢ Two-step screening strategy with 50 g GCT and 100 g OGTT with the Carpenter & Coustan criteria or the NDDG criteria

WHO: World Health Organization; ADA: American Diabetes Association; NIH: National Institute of Health; ACOG: American College of Obstetricians and Gynecologists; IADPSG: The International Association of Diabetes and Pregnancy Study Groups; GCT: glucose challenge test; OGTT: oral glucose tolerance test; NDDG: National Diabetes Data Group.

### The need for more research

Data from large prospective cohort studies using the IADPSG criteria in European populations are currently lacking. Moreover, there are no cost effective analysis data based on prospective studies in European populations comparing the IADPSG screening strategy with the two-step screening strategy. There are also no accurate data on the prevalence of GDM in Belgium and the current practice for screening for GDM varies across different centers [24]. The lack of consensus on screening for GDM is also apparent in Belgium. A recent Flemish consensus between endocrinologists, gynecologists and general physicians advises at this moment to continue with the two-step screening strategy while the recent consensus of the French-speaking obstetricians is to adopt the proposed IADPSG screening strategy for GDM [25,26].

Data on the impact of implementing the IADPSG criteria are currently based on retrospective analysis comparing the two-step screening strategy or the former WHO criteria with the IADPSG criteria. These studies generally show that women former classified normal and now GDM by the IADPSG criteria, have an impaired gestational outcome compared to the normal glucose tolerant (NGT) women [27,28]. We have previously shown that women prior classified normal by Carpenter and Coustan criteria and now GDM by the IADPSG criteria have increased rates of caesarean section and shoulder dystocia compared to the NGT group [29]. However, retrospective analyses comparing the former ADA screening strategy using a 100 g 3 h-OGTT with the IADPSG criteria have important limitations since comparisons were drawn on different sets of criteria (the 1-hour and 2-hour tests could therefore be higher than if a 75-g OGTT would have been used) and women identified by the IADPSG criteria as GDM but considered NGT using the Carpenter & Coustan were not treated. Moreover, women were not universally screened in early pregnancy to exclude an unknown overt diabetes. Retrospective analysis from our research group has also shown that 36.1% of GDM based on the IADPSG criteria, had a FPG meeting the threshold for GDM [30]. In contrast, using the IADPSG screening strategy in a large cohort of the United Arab Emirates, FPG independently could have avoided the OGTT in 50.6% of women [31]. This highlights the need to obtain data on GDM prevalence and data on the glucose measures that fulfill the diagnostic criteria with the IADPSG criteria in different populations as this will impact the strategy used for diagnosis of GDM.

### Objective and aims of the Belgian Diabetes in Pregnancy Study (BEDIP-N)

Since many uncertainties remain concerning the on-step IADPSG screening strategy for GDM, a large prospective multi-centric cohort study was designed. The overall objective of the Belgian Diabetes in Pregnancy Study (BEDIP-N) is to evaluate the impact of the IADPSG screening strategy on the prevalence of GDM and pregnancy outcomes in an ethnic diverse population.

Specific aims are:

➢ Aim 1: To evaluate the use of a GCT as an universal screening tool in a two-step approach with the use of the 75 g 2-hour OGTT with the IADPSG criteria only if the GCT is abnormal.

➢ Aim 2: By using a multivariable risk estimation model based on the most relevant clinical risk factors and biochemical measures for GDM, the aim is to develop a simple screening algorithm.

➢ Aim 3: To evaluate differences in GDM prevalence and pregnancy outcomes using different diagnostic criteria based on the 75 g OGTT: the IADPSG criteria, the Carpenter & Coustan criteria and threshold values if diagnostic criteria would be based on an odds ratio of 2.0.

➢ Aim 4: To explore the cost effectiveness of the one-step IADPSG screening strategy.

## Methods and Design

### Study design and setting

The BEDIP-N is a national multi-centric observational and prospective cohort study with the participation of 6 centers. The University hospital of Leuven (UZ Leuven) is the coordination center.

Women are universally screened for overt diabetes and GDM during the first trimester (recruitment <14 weeks but first screening test can be delayed until max. 16 weeks) by measuring the FPG. GDM in early pregnancy is defined as a FPG ≥100 and ≤125 mg/dl (≥5.5 and ≤6.9 mmol/l), in line with the definition of prediabetes outside pregnancy [23]. Overt diabetes in early pregnancy is defined as diabetes outside pregnancy [FPG ≥126 mg/dl (7.0 mmol/l)] [23]. The IADPSG recommendation that a FPG ≥ 92 mg/dl (5.1 mmol/l) in early pregnancy be classified as GDM was not adopted since more data are necessary on its validity. Using a higher FPG cut-off for GDM in early pregnancy will allow to evaluate the number of women with a FPG < 100 mg/dl (5.5 mmol/l) in early pregnancy to later develop GDM based on the 75 g OGTT with the IADPSG criteria.

Women without diabetes or GDM in early pregnancy, will be universally screened for GDM between 24–28 weeks of pregnancy, using the 50 g GCT and independently of the result of the GCT, will all receive the 75 g OGTT. The diagnosis of GDM will be based on the 75 g OGTT with the IADPSG criteria. Participants and researchers will therefore be blinded for the result of the GCT. The result of the GCT test will later be used to evaluate the use of a GCT in a two-step approach with the use of the 75 g OGTT with the IADPSG criteria only if the GCT is abnormal. Women with GDM, will be reevaluated three months postpartum with a 75 g OGTT using non-pregnancy diagnostic criteria. Women with diabetes or GDM will be treated according to a standardized protocol in line with current routine clinical practice.Data are collected during early and late pregnancy and at delivery and for women with GDM also at three months postpartum. At each visit blood samples are collected, anthropometric measurements are obtained and self-administered questionnaires are completed. Figure 1 gives an overview of the different steps of the study.

**Figure 1 F1:**
[figure not shown]
The different steps of the BEDIP-N study.

The Belgian National Lottery provides funding for this investigator-initiated study. The study is registered in ClinicalTrials.gov as NCT02036619. The study protocol was approved by the Institutional Review Boards of all participating centers (Belgian number: B322201420693).

### Study sample

#### Study cohort

The cohort is recruited from 6 centers: UZ Leuven, the University hospital of Antwerp (UZA), Imelda hospital Bonheiden, OLV hospital Aalst-site Aalst, OLV hospital Aalst-site Asse and St Jan hospital Brussels. Five centers are situated in the Northern part of Belgium: 2 centers in the province of Flemish-Brabant, 1 center in East-Flanders and 2 centers in Antwerp. One center is situated in Brussels, the capital city of Belgium. There is a good mix between centers with an average number of women from an ethnic minority background (BME) and centers with a high percentage of women from a BME background (St Jan Hospital Brussels and OLV hospital Aalst-site Asse). UZ Leuven and St Jan Hospital Brussels have a mean number of deliveries of 2200 per year and the other centers have between 700–1000 deliveries per year.

The aim is to enroll 2563 pregnant women in the first trimester over a 2 year recruitment period (see next paragraph for power calculation). The minimum recruitment planned per center is around 175 women per year (depending on the center between 100–300 women per year) with a max. of 25% of the pregnant population that has to be recruited. Recruitment began in April 2014 and will end around October 2016.

The expected duration of the study depends on the results of the screening tests during pregnancy. If a diagnosis is made of overt diabetes in early pregnancy or if no GDM is diagnosed early or later in pregnancy, the study will end when women and the baby leave the hospital after the delivery. For these women, the max. duration of the study will be 8 months. If women are diagnosed with GDM (early or later in pregnancy), an extra visit is planned three months after the delivery. For these women the expected duration of the trial will be max. 11 months.

#### Eligibility criteria

The inclusion criteria are:

• women 18–45 years

• a singleton pregnancy

• 6–14 weeks of gestational age

• viable pregnancy

• delivery planned in the hospital where the study is performed

The exclusion criteria are:

• < 18 years or > 45 year

• multiple pregnancy

• known diabetes or treatment with metformin

• non-viable pregnancy (miscarriage)

• chronic medical condition (uncontrolled hypertension, severe heart disease, severe chronic liver disease, severe chronic kidney disease, chronic infections such as HIV and hepatitis)

• bariatric surgery

• gastro-intestinal surgery changing the absorption of glucose (e.g. Billroth II)

• a normal follow up and treatment during pregnancy will not be possible (incompliance, psychiatric problems…)

• participating in another study 90 days before the start of the study

• planned home delivery or in a center not participating in the study

#### Power calculation and statistical analyses

We aim at demonstrating a higher proportion of macrosomia (birth weight >4 Kg) in women with GDM compared to women without GDM based on the IADPSG criteria. We assume that 5% of recruited women develop overt diabetes in early pregnancy and will be excluded from the analysis. We assume that 12.4% of eligible patients will develop GDM using IADPSG criteria (value as reported in ATLANTIC-DIP study) [28]. The prevalences of macrosomia for GDM and non-GDM cases used in the calculations are also based on results reported in the ATLANTIC-DIP study [28]. We calculate that the total number of subjects needed to demonstrate a difference in proportions of pregnancy complications with 80% power and 5% significance level, is 2563. The sample size calculation is based on a two-sided Chi-square test.

##### To analyze the overall objective and aim 3

The proportion of GDM cases with 95% confidence intervals will be estimated for both 2-step and one-step screening strategies. The difference in proportions between both screening strategies will be tested using McNemar’s test for paired proportions. McNemar’s test will be used for testing differences in proportions between Carpenter & Coustan criteria and IADPSG criteria, and between IADPSG criteria and diagnostic criteria based on an odds ratio of 2.0. All analyses will be performed using all valid measurements. The chi-square test for proportions will be used for the comparison of GDM and non-GDM patients on binary or categorical variables. The Mann–Whitney U test will be used in case both groups are being compared on ordinal or continuous variables. A complete case analysis will be performed including all cases for which both GDM status and characteristic or complication are observed.

##### To analyze aim 1

Sensitivity, specificity, positive predictive value and negative predictive value will be determined for the 50 g GCT as a predictor of the result of the two-step 75 g 2-hour OGTT. The analysis will be performed using all cases with valid measurements on both tests.

##### To analyze aim 2

Logistic regression models will be used with GDM as binary response variable and predictor as explanatory variable. Predictor-effects will be presented as odds ratios with 95% confidence intervals and p-values will be reported. Besides univariable analyses, a multivariable prediction model will be built, ultimately leading to a risk score definition for predicting the risk for developing GDM. A backward selection procedure will be applied for model building. A complete case analysis is planned, implying that all observations are used in the analysis for which all model variables are observed. In case of substantial missing data in predictor variables leading to power loss in the multivariable analysis, the technique of multiple imputation for dealing with missing data will be applied.

##### To analyze for aim 4

The economic evaluation will establish the cost-utility of the one-step IADPSG screening strategy from the health care payer perspective. To calculate QALYs, utility values of relevant health states (such as perfect health, GDM, preterm birth, permanent brachial plexus injury) are derived from the literature and combined with the time spent in the health state. Clinical data (such as the risk of preterm birth, the risk of GDM) are derived from the BEDIP-N study. Cost data are collected by the centers participating in the BEDIP-N study and are also extracted from the literature. The cost-utility is calculated as the cost per QALY gained in the base case analysis. A probabilistic sensitivity analysis is conducted to explore the robustness of cost-utility results to values of input parameters. Results of the probabilistic sensitivity analysis are presented on the cost-effectiveness plane and in a cost-effectiveness acceptability curve.

A 5% significance level will be adopted for all tests and all tests will be 2-sided. All analyses will be performed using SAS software, version 9.3 of the SAS System for Windows.

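### The three McNemar tests compare nested GDM classifications, so one discordant cell is zero by definition and the p-values say almost nothing about the size of the differences

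*Protocol article*

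**What the plan says.** All places are in the protocol article. Under Power calculation and statistical analyses, in the part on the overall objective and aim 3, the two screening strategies are compared as follows: "The difference in proportions between both screening strategies will be tested using McNemar’s test for paired proportions". The two comparisons of diagnostic criteria, the second of them against the odds-ratio-2.0 cut-offs, get the same method: "McNemar’s test will be used for testing differences in proportions between Carpenter & Coustan criteria and IADPSG criteria, and between IADPSG criteria and diagnostic criteria based". All tests are two-sided at 5%.

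The definitions behind the comparisons are these:

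- Two-step strategy (aim 1): a "two-step approach with the use of the 75 g 2-hour OGTT with the IADPSG criteria only if the GCT is abnormal".
- Testing at 24–28 weeks (Study design and setting): women without diabetes or GDM in early pregnancy are screened "using the 50 g GCT and independently of the result of the GCT, will all receive the 75 g OGTT".
- Aim 3 compares prevalence and outcomes "using different diagnostic criteria based on the 75 g OGTT: the IADPSG criteria, the Carpenter & Coustan criteria and threshold values" based on an odds ratio of 2.0.
- For that last set, the Background says "the threshold for abnormal values would have been higher" than the IADPSG ones.

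Estimates are also planned. The GDM proportions under the one-step and two-step strategies get 95% confidence intervals. Under aim 1, sensitivity, specificity and both predictive values of the GCT are to be determined. No interval for a paired difference is named for any pair.

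**The concern.** McNemar's test asks whether the two kinds of disagreement between paired classifications are equally frequent. That is a real question only if disagreement can go both ways. If one classification is a subset of the other, women can be reclassified in one direction only, and the test asks merely whether anyone is reclassified at all.

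At stake is the prevalence part of the overall objective and of aim 3. The useful question is how many women each alternative leaves undiagnosed relative to IADPSG. A p-value that is small both when few cases are lost and when many are lost does not answer it, yet it can be read as evidence that the difference matters.

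**Working it through.** **1. The plan's figures.** The article gives no power or size figure for the McNemar tests. Its 2563 belongs to the macrosomia comparison. The macrosomia rates are cited but not printed, so 2563 cannot be reproduced exactly; it is consistent, for example, with about 10% versus 15.6%. The counts needed here follow from stated inputs:

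- Analysed: 2563 × 0.95 = 2435 (5% overt diabetes excluded).
- IADPSG cases: 2435 × 0.124 = 302.

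**2. Nesting.** The cut-offs (mg/dl) come from Table 1 and the Background:

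| Criteria | Fasting | 1 h | 2 h | Abnormal values needed |
|---|---|---|---|---|
| IADPSG | 92 | 180 | 153 | 1 |
| Carpenter & Coustan (values available on the 75 g test) | 95 | 180 | 155 | 2 |
| Odds ratio 2.0 | 95 | 191 | 162 | taken as 1, as for IADPSG |

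Every alternative cut-off equals or exceeds the IADPSG one, and no alternative needs fewer abnormal values. Any woman positive under an alternative is therefore IADPSG-positive. A search over 313,600 combinations of the three glucose values found no exception, and a search in mmol/l found none either. Two-step GDM is an abnormal GCT together with IADPSG positivity on the same OGTT, so it is a subset of one-step GDM whatever GCT cut-off is used.

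**3. The test with one empty cell.** Let b be the number of women positive by IADPSG only and c the number positive by the alternative only, so c = 0.

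- Uncorrected chi-square: (b − c)²/(b + c) = b
- Continuity-corrected: (b − 1)²/b
- Exact two-sided: p = 2 × (1/2)^b

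| b | Uncorrected p | Corrected p | Exact p |
|---|---|---|---|
| 3 | 0.083 | 0.248 | 0.250 |
| 4 | 0.046 | 0.134 | 0.125 |
| 5 | 0.025 | 0.074 | 0.063 |
| 6 | 0.014 | 0.041 | 0.031 |

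Rejection starts at 4 women uncorrected (4/302 = 1.3% of cases) or 6 exact (6/302 = 2.0%).

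**4. Odds ratio 2.0.** The Background gives HAPO prevalences of 16.1% (IADPSG) and 8.8% (odds ratio 2.0). The share reclassified is (16.1 − 8.8)/16.1 = 45%. Scaled to the plan's cases, b ≈ 0.453 × 302 = 137, and exact p = 2 × (1/2)^137 ≈ 10⁻⁴¹.

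**5. The other two comparisons.** The article gives neither the GCT sensitivity nor the share of IADPSG cases that are Carpenter & Coustan negative, so the share s is an assumption shown over a range. With b ~ Binomial(2435, 0.124 × s):

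| Share s reclassified | Expected b | P(b ≥ 4), uncorrected rejects | P(b ≥ 6), exact rejects |
|---|---|---|---|
| 1% | 3.0 | 36% | 9% |
| 2% | 6.0 | 85% | 56% |
| 3% | 9.1 | 98% | 89% |
| 5% | 15.1 | >99.9% | 99.7% |
| 10% or more | 30 or more | ≈100% | ≈100% |

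**6. What an estimate shows.** With c = 0 the paired difference is d = b/n, with approximate 95% CI d ± 1.96 × √(d(1 − d)/n), n = 2435.

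- Odds ratio 2.0: 5.6 points (4.7 to 6.5).
- One-step minus two-step: 1.2 points (0.8 to 1.7) at an assumed GCT sensitivity of 90%; 2.5 (1.9 to 3.1) at 80%; 3.7 (3.0 to 4.5) at 70%.

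Separate intervals do not replace this. At 90% sensitivity they are 12.4% (11.1 to 13.7) and 11.2% (9.9 to 12.4). They overlap, although exact p for 30 discordant women is 2 × (1/2)^30 ≈ 2 × 10⁻⁹.

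**The case against.** The strongest reply is that the tests are redundant, not wrong. McNemar's test is valid for paired proportions, and no false conclusion would follow. The study is sized on macrosomia, and the chi-square and Mann–Whitney comparisons of women with and without GDM are unaffected. For the two-step comparison the informative quantities are largely planned: one minus the aim 1 sensitivity is the share of cases the GCT would miss, both proportions get intervals, and aim 4 adds a cost-utility analysis. All of this stands and keeps the point modest. It does not reach the two comparisons of criteria, where the McNemar test is the only prevalence comparison stated. Because the test is named for each pair, this is a stated choice and not a detail left to the analysis plan.

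A reader might infer more than the article supports:

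- That significance is guaranteed. The empty cell fixes the direction, not the p-value. If the GCT missed 2% of cases, the exact test would reject only about 56% of the time.
- That the study cannot show how many cases the GCT misses. Aim 1 reports exactly that.
- That an acceptable missed fraction must be fixed in advance. The article makes no non-inferiority or acceptability claim that would need a margin.
- That the Carpenter & Coustan result will be passed off as the 100 g, 3-hour prevalence. Aim 3 already says that the criteria are applied to the 75 g OGTT, so a labelling note is minor.

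**Conclusion.** The point holds as a weakness of moderate weight. The zero cell is exact in all three comparisons and needs no assumption about prevalence or GCT performance. That rejection is nearly certain rests on the planned size and the 12.4% prevalence. For odds ratio 2.0 it also rests on carrying over the HAPO ratio; applying the HAPO prevalences directly would give (0.161 − 0.088) × 2435 = 178 discordant women, on a different prevalence from the plan's, with the same conclusion. For the other two pairs it depends on a reclassified share that the article does not give, and rejection becomes uncertain only when that share is below about 5%. Above that, losing 5% of cases and losing 40% would both be reported as significant. The loss is of information, not of validity.

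**What to change.** In the part on the overall objective and aim 3, for each of the three pairs, replace the McNemar test, or demote it to a supplementary line, and report:

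1. the paired difference in GDM prevalence with a 95% CI (exact or score);
2. the proportion of IADPSG cases not identified by the alternative, with a 95% CI of the same kind. With 302 cases and an assumed 25% not identified, the half-width is about 1.96 × √(0.25 × 0.75/302) = 4.9 points.

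State that for the two-step strategy item 2 is one minus the aim 1 sensitivity, computed in the same women, so that the two results agree. A short table note can say that the Carpenter & Coustan cut-offs were applied to the 75 g test without a 3-hour value.

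The cost is a wording change in the protocol and analysis plan. It needs no new data, visits or participants, and the only thing given up is an uninformative p-value.
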